# Chemoembolization combined radiofrequency ablation vs. chemoembolization alone for treatment of beyond the Milan criteria viable hepatocellular carcinoma (CERFA): study protocol for a randomized controlled trial

**DOI:** 10.1186/s13063-023-07266-4

**Published:** 2023-03-28

**Keywords:** Hepatocellular carcinoma, Radiofrequency ablation, Transcatheter arterial chemoembolization, Randomized controlled trial

## Abstract

**Background:**

Many previous studies evaluated a combination of transcatheter arterial chemoembolization (TACE) and radiofrequency ablation (RFA) for treating early hepatocellular carcinoma (HCC); however, studies evaluating combination therapy for beyond-the-Milan criteria HCC are scarce.

**Methods:**

A total of 120 patients with beyond-the-Milan criteria HCC who have viable tumour after first TACE will be enrolled in this multi-institutional, parallel, pragmatic, randomized controlled trial. Patients with metastasis, vascular invasion, or a sum of tumour diameter > 8 cm will be excluded. Eligible patients will be randomly assigned to combination TACE and RFA therapy or TACE monotherapy groups. Patients in the combination therapy group will receive a second TACE and subsequent RFA at the viable tumour. Patients in the TACE monotherapy group will receive only second TACE. Patients in both groups will undergo magnetic resonance imaging 4–6 weeks after second TACE. The primary endpoint is 1-month tumour response, and secondary endpoints are progression-free survival, overall response rate, number of treatments until CR, overall survival, and change in liver function.

**Discussion:**

Although TACE can be used to treat intermediate-stage HCC, it is difficult to achieve CR by first TACE in most intermediate-stage patients. Recent studies show a survival advantage of combination therapy over monotherapy. However, most studies evaluating combination therapy included patients with a single tumour sized < 5 cm, and no studies included patients with intermediate-stage but more advanced (i.e., beyond-the-Milan criteria) HCC. This study will evaluate the efficacy of combined TACE and RFA therapy for patients with advanced HCC within the intermediate stage.

**Trial registration:**

Clinical Research Information Service (CRiS) KCT0006483.

## Administrative information

Note: the numbers in curly brackets in this protocol refer to SPIRIT checklist item numbers. The order of items has been modified to group similar items (see http://www.equator-network.org/reporting-guidelines/spirit-2013-statement-defining-standard-protocol-items-for-clinical-trials/).

## Introduction

### Background and rationale {6a}

Hepatocellular carcinoma (HCC) is the fifth most common cancer and the second leading cause of cancer-related mortality worldwide [1]. Although active surveillance programs and the widespread use of imaging have improved its early detection, HCC is often found at an advanced stage, and the outcomes of both local and systemic treatments are largely unsatisfactory. According to Barcelona Clinic Liver Cancer staging, the recommended treatment for HCC of an intermediate stage (B) is transcatheter arterial chemoembolization (TACE) [2]. However, the intermediate stage encompasses large heterogeneity in tumour size, number, location, and hepatic function. Although new chemotherapeutic agents have been developed, they still face many hurdles such as poor response rates, adverse events (AEs), and high overall costs. Although the benefits of locoregional versus systemic therapy remain controversial, locoregional therapy before systemic therapy is believed to be most effective for improving overall survival among non-surgically eligible patients [3].

Recent studies suggest that the combination of TACE and thermal ablation therapy is more effective than thermal ablation therapy alone [4–6]. However, these studies included patients with small (~ 3–5 cm), single tumours, whereas few studies have compared combination therapy versus TACE alone for intermediate-stage disease [7]. Also, the application of thermal ablation for large or multi-nodular HCC is technically difficult, as these types of tumours are prone to recur. Accordingly, few studies have evaluated local treatment for advanced-stage HCC. We postulate that combination of TACE and radiofrequency ablation (RFA) therapy could improve the rate of complete response (CR) and confer a survival benefit among patients with intermediate but beyond-the-Milan criteria. Although thermal ablation may not be applicable to large HCC, viable tumours after TACE are usually smaller than naïve tumours; thus, thermal ablation may also be applicable for viable tumours. The purpose of this trial is to compare 1-month tumour responses between patients with beyond-the-Milan HCC who receive combination TACE and RFA therapy versus TACE monotherapy.

### Objectives {7}

The primary endpoint is 1-month CR in patients with beyond-the-Milan criteria HCC who receive combination TACE and RFA therapy versus TACE monotherapy.

The secondary endpoints are:Progression-free survival durationObjective response rate (CR + partial response)Number of treatments until CROverall survival rates (6, 12, and 24 months)Change in liver function (i.e., Child–Pugh score) within 6 months

### Trial design {8}

This trial is a prospective, randomized, controlled, investigator-initiated, multi-institutional, open-blind, superiority study conducted in three academic hospitals of The Catholic University of Korea. Patient allocation will be performed with a 1:1 ratio for two parallel groups using computerized randomization.

## Methods: participants, interventions, and outcomes

### Study setting {9}

This multi-institutional randomized controlled trial will be conducted in three hospitals of The Catholic University of Korea: Seoul St. Mary’s Hospital, Eunpyeong St. Mary’s Hospital, and Incheon St. Mary’s Hospital. The study design is depicted in Fig. 1.

**Fig. 1 Fig1:**
[figure not shown]
CONSORT flow chart

### Eligibility criteria {10}

#### Inclusion criteria

Patients ≥ 19 years of age with an established diagnosis of HCC by radiologic study in high-risk patient groups (e.g., hepatitis B or C, alcoholism, autoimmune liver disease) or pathologic examinationSingle nodular HCC with a size of 5–8 cmDual nodular HCC with a maximal size of ≤ 8 cmTriple nodular HCC with a maximal size of ≤ 5 cmPatients meeting criteria (2) or (3) with viable HCC after first TACE^a^Child–Pugh score of ≤ 8No radiologic evidence of tumour invasion into the portal veinNo metastatic lesions outside the liverNo pathologic hematologic or renal functional abnormalities^b^ Eastern Cooperative Oncology Group performance score of 0 or 1

aViable HCC will be evaluated within 4–6 weeks after first TACE. Viable HCC should be treated within 4 weeks of radiologic evaluation after first TACE. Patients with longer treatment delays will be excluded from trial enrolmentbHaemoglobin > 8.5 g/dL, absolute neutrophil count > 750/µL, platelets > 30,000/µL, international normalized ratio ≤ 1.5, and serum creatinine level ≤ 1.5 mg/dL.

#### Exclusion criteria

Patients with grade ≥ 3 AEs according to the Common Terminology Criteria for Adverse Events (CTCAE) after first TACEUnfeasible location of viable HCC for RFAUncontrolled ascitesUncontrolled hepatic encephalopathyRecent variceal bleeding within 6 monthsPrior organ transplantActive gastric or duodenal ulcerOther uncontrolled comorbidities or malignant neoplasms (except for tumours with CR more than 5 years prior)Positive for human immunodeficiency virus Hematologic malignancy End-stage renal disease: patients not in a haemodialysis state (eGFR < 30 mL/min). Ongoing haemodialysis patients will be eligible for trial enrolment End-stage heart failure (New York Heart Association stage 3 or 4 or history of myocardial infarction within prior 12 months) Brain metastasis

### Who will take informed consent? {26a}

Informed consent will be obtained by investigators (i.e., hepatologists) in the outpatient clinic at each hospital after the first TACE. A detailed explanation of the trial and information sheets will be given to patients before obtaining their informed consent. No identifiable personal data will be published.

### Additional consent provisions for collection and use of participant data and biological specimens {26b}

We will request consent for review of participants’ medical records, and for the collection of blood samples to assess tumour markers (primary outcome) and liver function tests (secondary outcome). There will be no additional consent for ancillary studies.

### Interventions

#### Explanation for the choice of comparators {6b}

We hypothesize that tumour response will differ between patients with viable beyond-the-Milan HCC who receive combination TACE and RFA therapy versus TACE monotherapy.

### Intervention description {11a}

#### Before allocation

Patient eligibility will be evaluated after the first TACE. Patients with viable HCC after first TACE will be included in the trial. First TACE will be performed with ethiodized oil or drug-eluted beads with adriamycin (50–100 mg depending on tumour volume or liver function). The selection of ethiodized oil versus drug-eluted beads will be determined by discussion among physicians and interventional radiologists. All feeding arteries will be treated via superselective catheterization. Gelfoam particles will be used with ethiodized oil as is conventional for TACE.

#### Allocation

One month after first TACE, patients with viable tumour as revealed by computed tomography (CT) will be randomly allocated into combination therapy or monotherapy groups on the morning of the day of second TACE.

#### After allocation

All patients will undergo second TACE for the viable portion of the HCC with ethiodized oil and Gelfoam particles. Interventional radiologists performing second TACE will be blinded to patient allocation, and TACE will be performed in a conventional manner.

Patients in the combination TACE and RFA therapy group will be treated with additional RFA of the viable portion of the tumour under the guidance of fusion images from ultrasound and CT. RFA will be implemented within 1–2 days after second TACE. Whether RFA can be delayed for up to 1 month will depend on the medical condition of the patients. RFA will be performed by physicians at the three hospitals with more than 8 years of experience. A 17-gauge radiofrequency electrode system including three electrodes with a length of 150 mm and a 30-mm ablation zone (Octopus; STARmed, Goyang-si, Korea) will be used. The number of electrodes used will be determined based on the size of the viable tumour and the physicians’ discretion. However, physicians will attempt to obtain an ablation margin of at least a 1-cm perimeter around the viable tumour.

Patients in the TACE monotherapy group will be discharged from the hospital without further intervention if they experience no AEs.

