#### Follow-up and primary endpoint evaluation

All patients will be followed for 4–6 weeks after admission for second TACE on an outpatient basis. Magnetic resonance imaging (MRI) with gadoxetic acid (Primovist; Beyel-Shering Pharm, Beyel, Germany) and laboratory tests, including tumour markers and a liver battery, will be performed. Tumour response according to modified Response Evaluation Criteria in Solid Tumours (mRECIST) criteria will be assessed by two independent radiologists blinded to patient allocation (Asan Imaging Metrics, Seoul, Korea). In the case of disagreement, a third independent radiologist will review the imaging results and make a final decision.

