#### Criteria for discontinuing or modifying allocated interventions {11b}

Patients who are assigned to the combination therapy group and do not receive RFA within 2 days after second TACE without consent of the investigator will be excluded. However, RFA can be delayed up to 1 month for patients with severe post-embolization syndrome depending on the hepatologist’s discretion.

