#### Implementation {16c}

An independent statistician ([name]) will generate a stratified computer-generated block randomization list using STATA. A hepatologist will screen patients on an outpatient basis. If a patient agrees to participate in the trial, then the hepatologist will register the patient in the online database. Patients will be admitted to the hospital the day before second TACE. Second TACE will be performed by a dedicated interventional radiologist. After second TACE, patient allocation will be opened. According to their allocation, patients will be subsequently treated with RFA or discharged from the hospital.

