### Data collection and management

#### Plans for assessment and collection of outcomes {18a}

Consistent with the usual treatment course for HCC, initial laboratory tests and MRI will be performed. Tumour marker assessment (i.e., alpha-fetoprotein and protein induced by vitamin K absence-II) and MRI will also be performed 1 month after treatment. Blood laboratory tests and CTs will be performed depending on patients’ medical conditions as decided by the physician.

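### The primary-endpoint MRI is timed from second TACE, but RFA may follow up to 1 month later and nothing says how the MRI is then timed

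*Protocol article*

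**What the plan says.** All places are in the protocol article.

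- **MRI timing.** The Methods paragraph of the Abstract: "Patients in both groups will undergo magnetic resonance imaging 4–6 weeks after second TACE". Follow-up and primary endpoint evaluation starts the same window at admission: "All patients will be followed for 4–6 weeks after admission for second TACE on an outpatient basis". Implementation {16c} ties the two together: "Patients will be admitted to the hospital the day before second TACE".
- **RFA timing.** After allocation gives the plan, "RFA will be implemented within 1–2 days after second TACE", and then the exception, "Whether RFA can be delayed for up to 1 month will depend on the medical condition of the patients". Section {11b} repeats the exception on a narrower ground: "However, RFA can be delayed up to 1 month for patients with severe post-embolization syndrome depending on the hepatologist’s discretion".
- **Endpoint definition.** Outcomes {12} gives a 4–6-week CR with no starting point. Objectives {7} calls it 1-month CR.
- **Data collection {18a}.** "MRI will also be performed 1 month after treatment", without saying whether the treatment is TACE or RFA.
- **Participant timeline {13}.** Both intervention rows are marked in the 2 w column after allocation, and the follow-up MRI in the 1 m column. Yet the Allocation section places randomisation "on the morning of the day of second TACE".

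**The concern.** CR on this MRI is the sole primary endpoint. The MRI runs on a TACE clock, while the last assigned procedure in the combination arm can move by up to a month. Followed literally, the rules allow a delayed combination patient to be scored when only TACE has been given, or very soon after ablation.

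Only the combination arm can have such a delay. It arises after randomisation and is decided on the patient's condition, so time since last treatment would vary selectively within one arm. A later scan is not a clean substitute, because section {11d} allows other systemic or locoregional treatment once the primary endpoint has been evaluated. The unnamed treatment in {18a} and the table's 2 w column also leave sites room to schedule the scan differently.

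**Working it through.** The plan states no RFA-to-MRI interval, so there is no figure of its own to reproduce. The sample-size figures are not at issue here.

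**Inputs** (day 0 = second TACE)

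- MRI counted from TACE (Abstract): 4–6 weeks = day 28 to 42.
- MRI counted from admission (Follow-up section, with {16c} putting admission on day −1): day 27 to 41.
- RFA on schedule (After allocation): day 1 to 2.
- RFA at the permitted limit (After allocation; {11b}): 1 month, taken as day 28 to 31. The day count is an assumption, since the plan does not define a month.

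**Formula:** interval = MRI day − RFA day. A negative value means the MRI comes before RFA.

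| RFA day | MRI counted from TACE | MRI counted from admission |
|---|---|---|
| 1 | 28−1 = 27 to 42−1 = 41 | 26 to 40 |
| 2 | 26 to 40 | 25 to 39 |
| 14 | 14 to 28 | 13 to 27 |
| 21 | 7 to 21 | 6 to 20 |
| 28 | 0 to 14 | −1 to 13 |
| 31 | −3 to 11 | −4 to 10 |

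On schedule, the range over both clocks is 25 to 41 days. At full delay it runs from 3 days (TACE clock) or 4 days (admission clock) before RFA to 14 days after it.

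**When the MRI precedes RFA.** On the TACE clock this needs RFA on day 29–31 and an MRI on day 28–30, the first three days of a window that runs to day 42. Otherwise a fully delayed patient is read on the day of RFA or within the following 14 days.

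**Timeline table.** Interventions at 2 w (day 14) and MRI at 1 m (day 28–31) give 28−14 = 14 to 31−14 = 17 days. The text has allocation and second TACE on the same day and RFA 1–2 days later, so neither intervention belongs two weeks after allocation.

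**The alternative clock.** If the same 28–42 days were counted from a fully delayed RFA, the MRI would fall on day 28+28 = 56 to 31+42 = 73 after second TACE, against day 28–42 in the TACE-alone arm.

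**The case against.** The best defence is that delay is a limited exception. RFA is planned for day 1–2, section {11c} keeps both procedures in one admission unless severe post-embolization syndrome prevents it, and patients with grade 3 or worse adverse events after first TACE are excluded. A common clock from second TACE is also a legitimate choice for an intention-to-treat comparison, with any delay treated as part of the assigned strategy. Both points stand. They limit the severity, but they do not supply the missing rule for the MRI after a delayed RFA.

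Stronger readings that a reader might infer, and why the documents do not support them:

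- *Three incompatible time origins.* Admission is the day before second TACE and allocation is on its morning. These are one clock to within about a day, and the table's 1 m MRI column is compatible with it. Only the origin in {18a} is open, and it matters only when RFA is delayed.
- *CR will commonly be read before RFA.* That needs a near-maximal delay together with an MRI at the very start of its window.
- *All patients will be imaged about two weeks after treatment.* This takes the table alone against several sections of text. The 2 w label may mean a period rather than day 14. The column still contradicts the text, but as a labelling error.
- *A stated loss of CR difference or power.* Any such figure needs the share of patients delayed and imaged too early, and the documents give no basis for one.

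**Conclusion.** The point holds in a limited form and should be fixed. As written, the primary-endpoint MRI does not move when RFA is delayed, so a patient delayed the full month is read between about 3–4 days before and 14 days after RFA, instead of about 25–41 days after it. This rests on 1 month meaning 28–31 days and on the MRI being done within its stated window. Shorter delays shorten the interval in proportion: with RFA on day 14 it is 13–28 days. The number of patients affected is unknown and may be small, so the effect on the CR comparison cannot be sized. The unnamed treatment in {18a} and the table's intervention column are contradictions in the text whether or not any patient is delayed.

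**What to change.** Amend the protocol as follows.

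1. Reconcile the Abstract, After allocation, Follow-up and primary endpoint evaluation, {11b}, Outcomes {12}, the timeline {13} and {18a}, so that one origin and one window for the endpoint MRI are stated for both arms. The reading must not be able to precede or immediately follow an assigned RFA. In {18a}, name the treatment from which the month is counted.
2. State the trade-off behind the choice. A common clock from randomisation keeps the arms aligned in time, but protects the reading only if the window opens late enough after whatever delay is allowed. A clock from the last assigned procedure evens out the time since treatment, but images delayed patients later than the TACE arm (day 56–73 against day 28–42 at full delay).
3. Move the table's intervention marks to match the Allocation and After allocation sections.
4. Say that delayed patients are analysed in their assigned arm, as the Sample size section's intention-to-treat statement implies.

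After allocation and {11b} also give different grounds for delay and must be reconciled. Which delay is acceptable, and for whom, is for the sponsor's clinicians.

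Cost: amendment wording, a corrected table, and a later MRI for some patients (for all, if a common window is moved). No extra scan is needed. Recruitment is expected to run to about June 2026, so the change can still be made.

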#### Follow-up and primary endpoint evaluation

All patients will be followed for 4–6 weeks after admission for second TACE on an outpatient basis. Magnetic resonance imaging (MRI) with gadoxetic acid (Primovist; Beyel-Shering Pharm, Beyel, Germany) and laboratory tests, including tumour markers and a liver battery, will be performed. Tumour response according to modified Response Evaluation Criteria in Solid Tumours (mRECIST) criteria will be assessed by two independent radiologists blinded to patient allocation (Asan Imaging Metrics, Seoul, Korea). In the case of disagreement, a third independent radiologist will review the imaging results and make a final decision.

#### Criteria for discontinuing or modifying allocated interventions {11b}

Patients who are assigned to the combination therapy group and do not receive RFA within 2 days after second TACE without consent of the investigator will be excluded. However, RFA can be delayed up to 1 month for patients with severe post-embolization syndrome depending on the hepatologist’s discretion.

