#### Sample size {14}

A previous study reports that the rate of CR after combination TACE and RFA therapy was 53% for patients with HCC tumours > 5 cm [9]. By contrast, the CR rate after TACE monotherapy was 26% for patients with intermediate-stage HCC [10]. Thus, we assume that the difference in CR rate between groups may be 28%. In this trial, we calculated that 48 patients per group are needed to achieve a two-sided α level of 0.05 and statistical power of 80%. A total of 120 patients will be included in this trial (i.e., 60 patients per group) to account for a 20% dropout rate (PASS, version 16, NCSS statistical software). Data will be analysed on an intention-to-treat basis according to patients’ originally assigned group.

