#### Concealment mechanism {16b}

Informed consent will be obtained at the hepatology outpatient clinic. After agreeing to participate in the trial, patients will be admitted to the hospital based on its interventional radiology schedule. Random allocation will be performed on the day of second TACE. An outpatient hepatology clinic nurse who is independent from this trial will access the secure, password-protected, online database (i.e., REDCap) to perform patient allocation and notify the hepatologist only. All researchers and patients will be blinded to allocation status except for the hepatologist. Patient allocation will be released after the completion of second TACE.

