#### Methods in analysis to handle protocol non-adherence and any statistical methods to handle missing data {20c}

Data produced following protocol non-adherence will not be included in the trial and will be disclosed. All researchers will make an effort to reduce missing data to a minimum. We will handle missing data with multiple imputation (MICE Package, R ver. 4.0.3, The R Foundation for Statistical Computing, Vienna, Austria). Missing values will be handled appropriately following established guidelines [11].

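### The protocol promises intention-to-treat, but its missed-RFA exclusion and non-adherence rule take randomised patients or their data out of the primary CR analysis, probably to the combination arm's advantage

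*Protocol article*

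**What the plan says.** Three sections of the protocol article bear on who is counted in the primary comparison.

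- **Sample size {14}:** "Data will be analysed on an intention-to-treat basis according to patients’ originally assigned group".
- **Criteria for discontinuing or modifying allocated interventions {11b}:** combination patients who "do not receive RFA within 2 days after second TACE without consent of the investigator will be excluded". An allowance follows: "RFA can be delayed up to 1 month for patients with severe post-embolization syndrome depending on the hepatologist’s discretion". Intervention description {11a} likewise ties a delay to the patient's medical condition.
- **Protocol non-adherence and missing data {20c}:** "Data produced following protocol non-adherence will not be included in the trial and will be disclosed". The same section plans multiple imputation for missing data.

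On timing, Concealment mechanism {16b} states "Random allocation will be performed on the day of second TACE" and "Patient allocation will be released after the completion of second TACE". The hepatologist is told the allocation before that release. The primary test is a chi-square comparison of CR rates {20a}.

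**The concern.** An intention-to-treat analysis keeps each randomised patient in the assigned arm whatever treatment followed. A rule that removes patients because an allocated procedure was missed does the opposite, and {11b} can reach only the arm that has an RFA to miss. TACE-arm patients who would also have missed RFA stay in their denominator.

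Whether a late or missed RFA has consent, or is allowed as a delay, is decided once allocation is known. Blinded image reading does not protect against this, because it cannot restore patients who have been taken out.

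At stake is the primary endpoint of a 120-patient superiority trial. If the removed patients reach CR less often than the rest, the combination CR rate rises without any treatment effect.

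**Working it through.** **1. Order of events.** Randomisation and second TACE fall on the same day; allocation is opened after the TACE ({16b}, {16c}); RFA is then given or missed. Both removals therefore come after randomisation. The {11b} rule names only the combination group. The {20c} rule names no arm, but the only adherence criterion spelled out is the RFA one.

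**2. The plan's own figure.** Inputs from {14}: difference 28 points, two-sided alpha 0.05, power 80%, dropout 20%. Taking 54% against 26% to obtain 28 points, with the pooled normal formula:

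n = [1.96 × √(2 × 0.40 × 0.60) + 0.842 × √(0.54 × 0.46 + 0.26 × 0.74)]² / 0.28² = (1.358 + 0.559)² / 0.0784 ≈ 46.9, so 47 per group against the stated 48. Then 48 / (1 − 0.20) = 60 per group. The stated size reproduces to within one patient. (The cited rates, 53% and 26%, differ by 27 points rather than 28; that is a separate matter.)

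**3. Assumptions.** The documents do not give the share m of combination patients excluded or their CR rate q. I take m from 5% to 20%. The upper end equals the protocol's dropout allowance, which serves only as an anchor.

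**4. If the planning rates hold.** Completers 53%, TACE alone 26%. The analysis with exclusion reports 53 − 26 = 27.0 points. The intention-to-treat difference is (1 − m) × 53 + m × q − 26. With q = 26%, meaning that patients without RFA respond as TACE-alone patients do:

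| m | Combination CR, all randomised | ITT difference | Reported with exclusion | Overstatement |
|---|---|---|---|---|
| 10% | 0.90 × 53 + 0.10 × 26 = 50.3% | 24.3 | 27.0 | 2.7 |
| 20% | 0.80 × 53 + 0.20 × 26 = 47.6% | 21.6 | 27.0 | 5.4 |

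With q = 0 the overstatement is m × 53: 5.3 points at 10% and 10.6 at 20%.

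**5. If there is no true effect.** The CR rate is 26% in both arms as randomised. After exclusion the combination arm shows (26 − m × q) / (1 − m) on 60 × (1 − m) patients, against 26% on 60. Type I error is by exact enumeration of the uncorrected chi-square test, two-sided:

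| m | Patients left | q = 0%: apparent CR, type I error | q = 10%: apparent CR, type I error |
|---|---|---|---|
| 5% | 57 | 27.4%, 5.5% | 26.8%, 5.2% |
| 10% | 54 | 28.9%, 6.8% | 27.8%, 5.9% |
| 15% | 51 | 30.6%, 9.1% | 28.8%, 6.8% |
| 20% | 48 | 32.5%, 12.4% | 30.0%, 8.3% |

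The reference with 60 per arm and no exclusion is 5.2%. If q = 26%, the apparent rate stays at 26% and there is no bias.

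**The case against.** The strongest reply is that the rule is narrower than it looks. A reader might infer that every combination patient who misses the 2-day window is removed. The text does not say so: investigator consent keeps a patient in, and severe post-embolization syndrome allows a delay of up to 1 month. Nor can technically difficult tumours simply be assumed to drive the exclusions, since locations unfeasible for RFA are excluded before randomisation and both procedures are planned within one admission {11c}. What remains is mainly unapproved omission, such as refusal or scheduling, plus patients who never become fit for RFA. The documents say nothing about their number or prognosis. All of this stands. It argues for the lower end of the ranges and makes the direction of bias an inference: bias is nil if the excluded patients respond like the rest and would reverse if they did better. The {20c} rule also covers both arms, and its effect in the TACE arm cannot be predicted.

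A second reply is that the sections can be reconciled: {11b} does not say what the patients are excluded from, and data dropped under {20c} could be imputed, keeping everyone in the assigned group. This does not hold. Section {20c} says the data are left out, no section says that removed patients are imputed, and discarding an MRI result that was observed in order to impute it has no justification.

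**Conclusion.** The point holds as a conflict over the primary analysis population. Following the printed exclusions departs from the promised intention-to-treat analysis. Bias towards the combination is likely, not certain; it follows from the protocol's own premise that CR is more frequent with RFA than without.

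The size depends on two quantities that the documents do not give. At the planning rates, with 10% or 20% missing RFA and responding at 26%, the CR difference is overstated by 2.7 or 5.4 points. With no true effect at 26%, 5-20% excluded and 0-10% CR among them, type I error is about 5.2% to 12.4% against 5.2%; at 5% excluded the inflation is negligible.

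A reader might infer larger inflation, up to about 18%. That needs a common CR rate of 40%, which appears nowhere in the documents, together with a fifth of the arm excluded and no CR among them.

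The wording should be corrected before the data are analysed, because it decides who is counted.

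**What to change.** Reconcile {11b}, {14} and {20c} by naming one primary analysis set: every randomised patient, in the assigned group, whether or not and whenever RFA was given, with observed MRI results kept. Let the exclusions in {11b} and {20c} define only a secondary analysis labelled per-protocol. Restrict the stated multiple imputation to outcomes that are truly missing. Whether a patient without an evaluable MRI because of death or deterioration counts as not in CR is a separate design choice and is not needed here. The RFA timing rule itself is not changed by this.

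The cost is wording in the protocol and any analysis plan. The estimated effect may be slightly less favourable. In the 10% and 20% cases above, power with all 60 per arm analysed is about 0.79 and 0.69, against 0.87 at 53% versus 26% if everyone received RFA. That loss comes from missed RFA; excluding the patients would only hide it.
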